##### Message framing

Prior research has demonstrated that gain-framed messages (i.e., emphasize the benefits of quitting) may be more effective than loss-framed (i.e., emphasize the risks of persistent smoking) or non-framed (neutral) messages for encouraging smoking cessation [33, 34]. Within 1 month of receiving their LDCT-LCS results, participants receive a standardized message that emphasizes either the benefits of quitting (gain-framed) or the risks of continuing to smoke (loss-framed). Audio and video messages are pre-recorded by SCs and sent by email. For patients who do not have an email address, messages are sent via letter. A manipulation check assessing participant comprehension of the message framing intervention component is conducted.

### Training and treatment fidelity

To enhance the real-world generalizability of the trial findings, a trained SC from each LDCT-LCS site delivers the tobacco treatments. Several approaches are being used to enhance and measure fidelity to implementing enhanced standard care and the four treatment components following recommendations of the Treatment Fidelity Workgroup of the National Institute of Health Behavior Change Consortium [35, 36].

#### Initial training of LDCT-LCS SCs

All participating SCs receive 2.5-h didactic training in tobacco treatment via standardized webinar presentations led by one of the principal investigators and the research project associate. The webinar presentation covers the overall rationale for the integration of evidence-based smoking cessation in the context of lung cancer screening and specific training on the standard care provided for all CASTL participants as well as each of the 4 tobacco treatment enhancements being tested in the CASTL trial. The training includes information on the rationale for and proper use of NRT (lozenge and patch for the management of nicotine cravings and other symptoms of nicotine withdrawal). The training includes didactic training in brief MI and a demonstration video produced for the CASTL trial. SCs also receive an MI cessation counseling training manual that provides a detailed outline of recommended MI counseling sessions and are trained to complete an MI self-rating tool for each MI session conducted [37]. Lastly, each SC receives consultation regarding the development of an acceptable workflow individualized for routine LDCT-LCS referral to the quitline

During the CASTL trial, all participating SCs are invited to join twice monthly videoconference calls that cover presentation updates on the CASTL trial and SCALE collaboration, site recruitment, and pertinent reminders about protocol adherence and study implementation. The videoconference calls enable all participating SCs to have ongoing contact with the PIs and other members of the CASTL team and are intended to promote site retention and adherence to the study protocol.

#### Treatment implementation fidelity

The site coordinators document the delivery of the study interventions. Participants are also asked about the interventions they receive. To assess referrals to the Quitline, we obtain referral data from the SCs (e.g., fax referral forms). MSK research staff obtain a monthly utilization report from Arrowhead, the study-designated medication dispensary. This includes information such as which patient received NRT, when it was ordered, the exact package contents, and other usable data points. Study participants are also asked to keep a medication log to monitor NRT usage and use is assessed during the 3-month survey collection. SCs follow an MI treatment manual and provide self-assessments for MI adherence for those participants assigned to the MI condition [37]. Finally, the study staff document the distribution of the message framing letter and/or scripted video/audio.

### Data sources and timing of data collection

Data is collected from participating SCs and persons who currently smoke and are seeking lung cancer screening. Baseline SC surveys are completed prior to recruiting participants at their LCS sites. Following completion of target enrollment at each site, SCs complete a follow-up survey and a semi-structured interview. They also complete a semi-structured interview for the PACT ancillary study to assess recruitment practices during their active recruitment period for CASTL.

Baseline surveys are collected from eligible and consented participants prior to randomization. Two follow-up assessments are completed: the first occurring approximately 3 months and the second occurring approximately 6 months following randomization. Depending upon patient preference, surveys are being completed by phone (with an MSK research team member), by email (via REDCap), or by paper (by mail). Patient participants receive a $25 incentive for each assessment completed, including the return of the saliva sample for biochemical verification of smoking abstinence. Members of the MSK research team, including the data analysts are not blind to the treatment assignment. Data collection measures are listed in Table 2. To minimize attrition, participants receive a combination of up to six reminder phone calls, and/or emails, based upon their preference, for follow-up data collection. Participants who are unreachable after these attempts are mailed a hard copy of the survey for completion.

**Table 2 Tab2:** Measures

Domains	Patient assessment				Site coordinator assessment		Instruments
	Baseline	3 months	6 months	Biochem	Baseline	Follow-up and interview	
Demographics							
Age, gender, race, ethnicity, education, marital status, SES, employment status^a^, income^a^	X				X		
Health literacy	X						BRIEF [38]
General health							HINTS [39] EQ 5D [40] Charlson Comorbidity Index [41]
Physical health	X						
Medical co-morbidities	X						
Family history of lung cancer	X						NLST [42]
Smoking history/current Tob. use							Heaviness of Smoking Index [43]
Cigarettes per day	X	X	X				
Current smoking	X	X	X				
Current use of other tobacco products	X						
Quitting history and methods used	X	X	X				
Behavioral health							K6 [44] Audit-C [45] CDE: 3600797 [46]
Depression	X	X	X				
Alcohol use	X						
Drug use	X						
Perceived risk							Risk Perception [47]
Personal and comparative risk	X	X	X				
Worry	X	X	X				
Beliefs about benefits	X	X	X				
Smoking cessation beliefs							Contemplation Ladder [48] Quitting Confidence [34] ANRT-12 [49] ISSI [50]
Readiness to quit	X	X	X				
Quitting motivation	X	X	X				
Self-efficacy	X	X	X				
Attitudes towards NRT	X						
Smoking stigma	X						
Treatment utilization and satisfaction							
NRT use		X	X				
Quitline use		X	X^b^				
Patient satisfaction		X	X^b^				
COVID-19							
Changes in motivation	X	X	X				
Changes in smoking	X	X	X				
Abstinence							
~ 3 months abstinence and 7-day prevalence		X	X				
24 h quit attempt							
Smoking reduction (50%)		X	X				
Verification of abstinence		X	X	X			
Site characteristics							
Payor mix, affiliation, screening history, % of current smokers					X	X	
Current cessation services					X	X	
Organizational priority and feasibility^c^							Organizational priority Implementation outcome Clinical Sustainability Assessment Tool [51]
Priority (readiness and barriers)					X	X	
Appropriateness and feasibility					X	X	
Sustainability						X	

^a^Not collected from site coordinators

^b^Assessed at 6 months if the 3-month survey is missed

^c^Also assessed during a semi-structured interview

### Participant surveys

Assessments developed for the study included a combination of core and opt-in items agreed upon by the members of the SCALE collaboration in addition to study-specific items [52]. Data collected from the core and opt-in items from all SCALE projects is shared with the NCI periodically and pooled to be used in cross-project collaborations.

#### Baseline variables

Our baseline assessment includes measurement of demographic characteristics (age, gender, race, ethnicity, education, marital status, education, and SES), perceived health risks (personal and comparative), worry about lung cancer, current and smoking history (frequency, number of cigarettes smoked, age of the first cigarette and current use (in the past 30 days) of other tobacco products including e-cigarettes). We also assess participants’ health literacy, self-reported physical health, medical comorbidities, family history of lung cancer, behavioral health (depression, alcohol, and illicit drug use), smoking cessation beliefs (readiness and confidence to quit, importance of quitting, and attitudes about NRT and stigma). We also added an assessment of changes in motivation and rates of smoking resulting from the COVID-19 pandemic. This collection of variables will allow us to characterize the sample and investigate moderators of treatment outcomes.

#### Process variables

SC fidelity [35, 36] to the study interventions is monitored through a review of treatment logs completed for each participant and entered via REDCap. This includes the length of time spent on each intervention, a checklist of topics discussed with the participant, and confirmation of a Quitline referral. We also collect self-reported treatment utilization data (e.g., use of NRT, receipt of interventions and services received through the Quitline) and assess satisfaction with the interventions received during the 3-month follow-up assessment [53]. Patients who do not complete the 3-month assessment are asked the satisfaction questions at 6 months.

#### Primary outcome

The primary outcome of CASTL is biochemically verified abstinence (cotinine levels reflect recent nicotine exposure) at 6 months post-randomization. Participants reporting a 7-day point prevalence abstinence at the 6-month follow-up are asked to submit a saliva sample (via mail) for analysis [54]. Consistent with intent-to-treat (ITT), unless self-reported smoking abstinence is biochemically verified, for participants who fail to return the saliva sample, the cessation outcome will be considered non-abstinent. We selected 7-day point prevalence abstinence since it is biochemically verifiable and highly correlated with continuous and sustained abstinence [55]. Salivary cotinine values of ≥ 3 ng/ml, 1 to < 3 ng/ml, and < 1 ng/ml and cotinine levels of 31.5 ng/ml, 1 to < 31.5 ng/ml, and < 1 ng/ml are consistent with active, passive, and no smoking exposure, respectively [55]. Saliva specimens are collected using mailing kits from study participants reporting smoking abstinence and sent back via overnight mail to the lab for the measurement of cotinine concentrations using an established competitive enzyme-linked immunosorbent assay (ELISA). As an alternative, we also request contact information for a proxy [56], someone who is able to confirm the participant’s abstinence in the absence of a biochemically verified sample. Participants who decline to return a saliva sample or are not confirmed abstinent by their proxy will be considered persons who smoke per ITT.

#### Secondary outcomes

In addition to the primary outcomes, secondary cessation outcomes will be self-reported 7-day point prevalence abstinence at 3 months, continuous abstinence (between the date of randomization and date of completion of follow-up surveys) at 3 and 6 months, self-reported 24 h quit attempt and reduction in cigarettes per day (cpd), changes in quitting motivation and confidence, and changes in depression and perceived smoking risk at 3 and 6 months [34, 52, 57].

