### Study aims

#### Aim 1

To identify which of four evidence-based tobacco treatment components contribute to superior cessation endpoints among people who currently smoke and are seeking lung cancer screening over and above enhanced standard care (i.e., minimum intervention needed for change). The four tobacco treatment components being tested are (1) motivational interviewing (MI) (yes vs. no), (2) nicotine replacement therapy (NRT) patch (yes vs. no), (3) NRT lozenge (yes vs. no), and (4) message framing (gain vs. loss). We hypothesize that all four treatment component enhancements will be statistically superior to enhanced standard care alone and that some synergistic treatment component effects will emerge. For the message framing condition, we expect that gain-framed messages will result in higher quit rates. The primary cessation outcome is biochemically verified 7-day point abstinence at 6 months following study enrollment. Secondary cessation outcomes are self-reported 7-day point prevalence abstinence at 3 months, continuous abstinence (between the date of randomization and date of completion of follow-up surveys) at 3 and 6 months, and self-reported 24-h quit attempt at 3 and 6 months.

#### Aim 2

To estimate the cost and incremental cost-effectiveness of evidence-based tobacco treatment components, delivered alone and in combination.

#### Aim 3

To conduct a robust, mixed methods evaluation of the implementation process and assess site characteristics and organizational factors that may influence the implementation of tobacco treatment in lung cancer screening settings.

#### Aim 4

To analyze whether lung cancer screening results (i.e., Lung-RADS®) moderate smoking abstinence outcomes. We hypothesize that participants found to have one or more screening abnormalities will be more likely to quit smoking and maintain smoking abstinence.

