### Patient eligibility

Consistent with the 2013 USPSTF recommendations for LDCT-LCS, eligible patient participants are between [27] the ages of 55–80 years old (at the time of their LDCT scan), seeking baseline or annual follow-up LDCT-LCS, have at least a 30-pack-year history of smoking, currently smoking (defined as self-reported cigarette smoking on some days or every day) within the past 30 days, reachable by telephone, and English speaking. In April 2021, the eligibility criteria were expanded to include patients who were between the ages of 50–80 years old (at the time of their scan), with at least a 20-pack-year history of smoking. To facilitate the inclusion of non-English speaking participants, the study materials were later translated into Spanish and Spanish-English bilingual staff were hired. Patients are excluded from participation if either nicotine replacement therapy (NRT) is medically contraindicated (e.g., recent heart attack within the last 2 weeks) or they presented severe medical or psychiatric comorbidities that may prevent them from participating fully in the study (per the discretion of the screening SC or the study’s principal investigators). Finally, patients who are receiving concurrent tobacco treatment services or have used cessation medications (NRT, bupropion, varenicline) within the past month with the intent to quit smoking are excluded. Black people who smoke who actively or passively refused participation in CASTL are approached for participation in the ancillary refusal study.

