### Patient randomization and assignment to treatment group

Eligible patients who smoke are registered via MSK’s Clinical Trials Management System to the CASTL trial and randomized using the Clinical Research Database by a CRC. Individual study participants are randomized to one of the 16 intervention combinations listed in Table 1. Randomization is stratified using the method of the random permuted block by participating LDCT-LCS site. After patient registration and randomization, a designated MSK CRC sends each SC a secure email containing the patient’s treatment assignment.

**Table 1 Tab1:** Treatment components

Components					
Conditions	Enhanced standard care	Motivational interviewing	NRT lozenge	NRT patch	Message framing
**1**	Yes	Yes	No	No	Loss
**2**	Yes	Yes	No	No	Gain
**3**	Yes	Yes	No	Yes	Loss
**4**	Yes	Yes	No	Yes	Gain
**5**	Yes	Yes	Yes	No	Loss
**6**	Yes	Yes	Yes	No	Gain
**7**	Yes	Yes	Yes	Yes	Loss
**8**	Yes	Yes	Yes	Yes	Gain
**9**	Yes	No	No	No	Loss
**10**	Yes	No	No	No	Gain
**11**	Yes	No	No	Yes	Loss
**12**	Yes	No	No	Yes	Gain
**13**	Yes	No	Yes	No	Loss
**14**	Yes	No	Yes	No	Gain
**15**	Yes	No	Yes	Yes	Loss
**16**	Yes	No	Yes	Yes	Gain

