##### Enhanced standard care

SCs provide all CASTL participants with self-help, print cessation materials targeting persons who currently smoke seeking lung cancer screening, *Why Quit Now? A Resource for Those at Risk for Lung Cancer* [28] and refer patients to the national Quitline at [name] for education and follow-up cessation counseling during their first session within 1 month of randomization or during the shared decision-making discussion. Enhanced standard care was chosen as the comparator to ensure that at minimum, all participants receive cessation advice and an active referral to the Quitline, a service that was not consistently provided to participants prior to CASTL.

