##### Motivational interviewing (MI) [29]

There is substantial evidence that even brief MI can increase adherence to tobacco treatment and quit rates [30]. Participants assigned to the MI component receive two MI counseling sessions delivered by the SC; the first delivered face to face or via telephone during the patient’s lung cancer screening visit, and the second session, delivered via telephone by the SC approximately 1 to 8 weeks after participants receive their LDCT scan results. In response to the difficulties reaching patients during the COVID-19 pandemic, we amended the protocol to allow SCs to deliver the first session of MI (including the enhanced standard care) within 1 month of the participant’s randomization to the study.

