### Limitations

Careful consideration was given to potential pitfalls and methodological challenges that may be encountered during the proposed project. First, we recognize the concern about potential treatment contamination and have taken several steps to ensure that participants receive the treatment package consistent with their random assignment. Random assignment of patients to treatment conditions is conducted centrally by the MSK Coordinating Center and the appropriate treatment components are mailed to participating patients and their SC is informed of the assignment by email. We will also assess implementation fidelity with several sources of triangulated data. Third, given that CMS required that persons who currently smoke receive information about treatment for tobacco dependence, we decided to evaluate potential tobacco treatment component enhancements against a high quality, enhanced standard of care rather than a no treatment control. Finally, we considered several alternate treatment components and eliminated tobacco treatment options unlikely to be feasible (e.g., prescription medications) or sustainable (intensive group or individual counseling) in most LDCT-LCS settings. It is plausible that more intensive tobacco treatment components may be needed to achieve clinically meaningful cessation outcomes and long-term smoking abstinence.

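### Continuous abstinence is counted from randomization, so a quit prompted by a component that arrives later is scored as failure on this secondary outcome

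*Protocol article*

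**What the plan says.** Aim 1 lists as a secondary outcome "continuous abstinence (between the date of randomization and date of completion of follow-up surveys) at 3 and 6 months". The Secondary outcomes section repeats the definition: "continuous abstinence (between the date of randomization and date of completion of follow-up surveys". Neither place gives a grace period.

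Under Patient eligibility, participants must be "currently smoking (defined as self-reported cigarette smoking on some days or every day) within the past 30 days". The section on randomization sets the order of events: "After patient registration and randomization, a designated MSK CRC sends each SC a secure email" with the assignment. The Limitations section adds that "the appropriate treatment components are mailed to participating patients and their SC is informed of the assignment by email". Lozenges and patches come by mail.

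Enhanced standard care is given "during their first session within 1 month of randomization or during the shared decision-making discussion". Under the pandemic amendment, coordinators may "deliver the first session of MI (including the enhanced standard care) within 1 month" of randomization. The second session follows "approximately 1 to 8 weeks after participants receive their LDCT scan results". The framed message is due within 1 month of those results.

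Participant recruitment and Trial status now allow enrollment from 60 business days before the scan to 60 business days after it. The follow-up surveys are at about 3 and 6 months after randomization.

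**The concern.** Aim 1 asks which components produce quitting beyond enhanced standard care. An outcome that answers this must be able to register a quit that a component brings about. This one starts before any randomized component can have reached the participant. Read as written, it credits a component only with keeping abstinent those who had already stopped by the day of randomization. A smoker who stops when the patches arrive, or after the first session, and never relapses is counted with those who never tried.

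Real component effects would therefore look smaller on continuous abstinence than they are. A null result there could be taken as evidence that a component does not support lasting abstinence.

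A smaller issue concerns delivery. The enrollment window was widened after the scan, but the article states the message and second-session windows only relative to scan results. Some permitted enrollment dates fall after those windows have closed.

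**Working it through.** **No plan figure to reproduce.** The article gives no number for this outcome. Its power statement (85%, two-sided 5%, 0.20 SD, 20% attrition) concerns the primary aim. It reproduces: 1152 × 0.8 / 2 = 460.8 per level gives 85.9%. Nothing here changes it.

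**Order of events**, with randomization as day 0:

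| Randomized component | Route | Timing after day 0 |
|---|---|---|
| Patch, lozenge | Mailed after assignment | Later than day 0; transit time not stated |
| MI session 1 | Coordinator, once told of the assignment | Up to about day 30 under the amended rule |
| Framed message | Sent after scan results | After assignment; for early pre-scan enrollees, well past day 30 |
| MI session 2 | Telephone, after scan results | As for the message, and later |

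Enhanced standard care may be given at the shared decision-making discussion and so could precede randomization. All conditions receive it, so the point concerns only the four randomized components.

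**Scoring example.** A participant smokes until a first session on day 30, then quits and stays quit. With surveys at about days 91 and 182:

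- Days abstinent by each survey: 91 − 30 = 61 and 182 − 30 = 152.
- Seven-day point prevalence: abstinent at both surveys.
- Continuous abstinence from randomization: failed at both surveys.

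Share of each period that may pass before the first session: 30/91 = 33% and 30/182 = 16%. These are ceilings, because the session may come sooner and mailed nicotine replacement may be started earlier.

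**Longest waits for the later contacts.** 60 business days = 60/5 × 7 = 84 calendar days, ignoring holidays. The article gives no delay d from scan to results; I assume 0 to 14 days. For someone enrolled 84 days before the scan:

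- Latest message: 84 + d + 30 = day 114 to 128.
- Latest MI session 2: 84 + d + 56 = day 140 to 154.

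Both lie beyond the 3-month survey and inside the 6-month period.

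**Delivery windows for post-scan enrollees**, in days after the scan:

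- The message window closes at d + 30 = 30 to 44. That leaves 84 − 44 = 40 to 84 − 30 = 54 enrollment days outside it (40/84 = 48% to 54/84 = 64%).
- The session 2 window closes at d + 56 = 56 to 70. That leaves 14 to 28 days outside it (14/84 = 17% to 28/84 = 33%).
- The overlap problem disappears only if d is at least 84 − 30 = 54 days (message) or 84 − 56 = 28 days (session 2).
- The former limit of 7 business days (9 to 11 calendar days) lay inside both windows.

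These are shares of the calendar. The share of participants is not known.

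**The case against.** **On the outcome.** The definition is explicit, is the same in both places, and applies to every condition, so it biases no contrast. It is one strict measure beside point prevalence, quit attempts and smoking reduction. The primary outcome, 7-day point prevalence at 6 months, catches later quitters. Scoring detail such as a grace period can be left to a full protocol or analysis plan. All this limits the weight of the point but does not remove it. The start date is a stated rule, not an omitted detail, and it works against the question that the outcome serves. Table 2 lists an item on about 3 months of abstinence at both follow-ups. At 6 months that item does not clearly match a count from randomization, so the two need reconciling anyway.

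**On the windows.** A reader might infer that late post-scan enrollees miss the message or second session, and that the message and MI effects on the primary outcome are diluted. The document does not support this. No section withholds a component once its window has closed. The section on criteria for removal says that allocated interventions are otherwise left unchanged, the session 2 window is only approximate, and study staff may deliver interventions if needed. Late delivery is the natural reading. The article also condenses a fuller protocol, and its list of modifications is not complete: it omits the session 1 change reported elsewhere. What stands is that two sentences do not fit the widened enrollment window.

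**Conclusion.** The point holds as a minor one about a secondary outcome. As defined, continuous abstinence at 3 and 6 months cannot register a quit that follows the arrival of a randomized component, so component effects on it are attenuated. The rule is identical in all 16 conditions, so no level is favored. The size of the attenuation cannot be computed from the document, because the timing of quits is unknown. The 33% and 16% are upper limits on the wait for the first session, not effect sizes. The primary outcome and 3-month point prevalence are untouched.

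The window mismatch is a wording correction. Its dates are right, but the calendar shares rest on an assumed results delay of 0 to 14 days, and no effect on the primary outcome is established.

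**What to change.** **Outcome.** Define it as sustained abstinence after a fixed grace period, equal in all 16 conditions: for example, no smoking from day 31 to the survey. This needs a quit or last-smoking date. Table 2 lists quitting history at both follow-ups, but the item wording is not shown. A day-31 start would still precede the message and session 2 for people enrolled well before the scan. At 6 months the abstinence item already in Table 2 is an alternative: it covers about months 3 to 6, allows for most of those contacts and needs no new data. Keep the count from randomization as a sensitivity analysis. The cost is one definition and slightly less comparability with trials that count from day 0. The article places analysis after data collection ends, so the change can still be prespecified.

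**Windows.** For remaining enrollees, time the message and MI session 2 from the later of scan results or randomization, with session 2 after session 1. This costs two sentences and an IRB amendment. It reaches fewer than 1152 − 734 = 418 participants, since the article says the target will not be met.
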